### Objectives

#### Primary objective

Four types of transfer training interventions have been described: strategy-based (e.g., logical reasoning), multimodal (complex, often social or lifestyle interventions), cardiovascular (i.e., physical training), and specific cognitive process-targeted training interventions (e.g., working memory) [16]. Transfer effects differ between transfer types but share a common feature: transfer effects decline with age [16]. To date, little is known about the neural mechanisms of transfer [16]. Specifically, the mechanisms of either maintenance or age-related decrease of transfer of cognitive training gains in HOA are largely unknown. Increased bihemispheric cooperation can reliably be seen with increasing processing demands in young adults and, as we showed, already on lower levels of cognitive demand in HOA [17]. This compensatory increase of bihemispheric processing in HOA is known as the concept of Hemispheric Asymmetry Reduction in Older Adults (HAROLD) [12]. This phenomenon could be the functional link between the observed association of transfer capabilities and structural integrity of the corpus callosum. Beyond pure compensation, HAROLD may serve as a mechanism enabling the structurally and functionally altered aged brain to use alternative neural circuitry and thereby to re-establish more efficient lateralized processing during learning [16]. Hence, increased bihemispheric cooperation/HAROLD, based on the structural integrity of the corpus callosum, may indeed be a functional mechanism mediating transfer capabilities in HOA.

Main research goal of the AgeGain study is to investigate the neurobiological mechanisms of transfer of cognitive training gains in detail by elaborating brain network capabilities representing transfer using a multimodal-neuroimaging approach in HOA. Specifically, the following primary hypothesis will be tested: Structural integrity of the corpus callosum (high / low) and bihemispheric cooperation (reduced / increased) will predict successful transfer of cognitive training gains in HOA. The association of corpus callosum integrity with transfer capability will be determined by diffusion-tensor imaging (DTI) measures of structural integrity / connectivity, mainly fractional anisotropy (FA) of the corpus callosum, see Fig. 2a. The association of bihemispheric processing and transfer capability will be determined using task-related functional magnetic resonance imaging (fMRI) (see Fig. 2b).

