**Fig. 2 Fig2:**
[figure not shown]
Joint models of brain structural (**b**) and functional (**a**) mechanisms for the explanation of transfer capability in healthy aging. **a** Fractional anisotropy (FA) of the genu and corpus of the corpus callosum decreases with age in cognitively healthy elderly; higher FA values indicate better structural integrity. Structural integrity of the corpus callosum predicts transfer capability determined by stable success (ST) versus non-transfer (NT) [11]. Categorial transfer was defined as an increase of fluid intelligence performance (transfer task) beyond the retest effect of untrained healthy elderly after successful training of logical reasoning skills [11]. Taken the corpus callosum structural integrity (FA) as surrogate of transfer capability, the model delineates a threshold of structural integrity (− − −) dividing ST and NT. Moreover, the model suggests that (e.g., z-standardized) FA values could be taken as dimensional predictors of the transfer amount in single subjects. **b** Increased hemispheric cooperation/HAROLD as measured by BOLD lateralization index [70] may mediate transfer capabilities in older adults since both are associated with the structural integrity of the corpus callosum. NT subjects may show less hemispheric cooperation compared to ST subjects at baseline thereby predicting less transfer success while both groups show the general pattern of lateralized to bilateral to disengagement of activity with increasing task demand [17]

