#### Analysis of secondary endpoints

For evaluating physical training as potential modulator of cognitive training gain transfer, correlations between fitness changes and integrity changes of the corpus callosum will be applied. Moreover, an interaction between corpus callosum integrity and fitness changes with respect to transfer will be considered in a logistic regression model. Such an interaction can be expressed as a correlation between fitness changes and the degree of transfer in a group with low/high corpus callosum integrity.

To evaluate the predictive value of brain vascular lesion, cortical amyloid load, higher Default Mode Network activity, and genetics for transfer of cognitive training gains in HOA, a logistic regression model with transfer as the dependent variable is used. All effects of the potential predictors are included as main effects. Additionally, to adjust for ACT, ACT and all interactions with ACT are included in the model as independent covariates.

To determine the impact of ACT on the structural integrity of the corpus callosum, Default Mode Network activity, BDNF, motor fitness, and VO_2_peak/VO_2_max, logistic regression models for these variables are fitted. ACT will be included as an independent variable. Additionally, the model will be adjusted for all other variables and the interactions with ACT. For example, the model for structural integrity of the corpus callosum will include ACT, Default Mode Network activity, BDNF, motor fitness, VO_2_peak/VO_2_max and all interactions with ACT as independent covariates.

Similar models will be fitted to examine the association between baseline physical activity and the structural integrity of the corpus callosum, Default Mode Network activity, and BDNF. Here, baseline physical activity and all possible interactions with baseline physical activity will be additionally included as independent covariates.

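### The models for the effect of ACT and of baseline physical activity are specified as logistic regressions, although their dependent variables are quantitative and no cut-off is stated

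*Protocol article*

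**What the plan says.** The third paragraph of *Analysis of secondary endpoints* (Protocol article, Statistics) sets out how the impact of ACT will be determined on five variables: callosal structural integrity, Default Mode Network activity, BDNF, motor fitness and VO2peak/VO2max. The method is "logistic regression models for these variables are fitted. ACT will be included as an independent variable". The worked example settles which side of the equation these variables are on: "the model for structural integrity of the corpus callosum will include ACT, Default Mode Network activity, BDNF, motor fitness", together with oxygen uptake and the interactions with ACT. Integrity is therefore the dependent variable in that model, and each of the other four takes its turn.

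The next paragraph extends the approach: "Similar models will be fitted to examine the association between baseline physical activity and the structural integrity of the corpus callosum", and likewise for Default Mode Network activity and BDNF.

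On scale, *Primary objective* says that integrity will be determined by "diffusion-tensor imaging (DTI) measures of structural integrity / connectivity, mainly fractional anisotropy (FA) of the corpus callosum". The legend of Fig. 2 adds that "FA values could be taken as dimensional predictors of the transfer amount in single subjects".

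**The concern.** Ordinary logistic regression models the probability of a binary event. Fractional anisotropy, a connectivity measure, a serum level, motor test scores and an oxygen uptake are not binary. An analyst who follows the text has to change the model or cut each outcome in two, and the article does not say where to cut.

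Three things are at stake. A cut discards information. A cut-point that is not fixed beforehand can be chosen after the data are seen. And the result is an odds ratio for being above a threshold, whereas the question is how much integrity, BDNF or oxygen uptake differs with ACT. The Abstract names these five variables as the trial's secondary endpoints, so the wording matters.

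**Working it through.** **Step 1: scale of each outcome, from the article.**

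| Outcome in the ACT models | How the article describes it | Binary rule given? |
|---|---|---|
| Callosal integrity | Fractional anisotropy from DTI, called dimensional and open to z-standardization (*Primary objective*; Fig. 2 legend) | High/low label elsewhere, as predictor or subgroup only; no cut-off value |
| Default Mode Network activity | Resting-state fMRI connectivity (*Secondary objectives*) | No |
| BDNF | Levels (*Secondary objectives*) | No |
| Motor fitness | Test batteries (*Fitness examinations*) | No |
| VO2peak/VO2max | Oxygen uptake estimated from a 6-minute walking test (*Fitness examinations*) | No |

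The only outcome defined as Yes/No is transfer (*Definition and analysis of primary endpoint*).

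**Step 2: consistency within the section.** The first paragraph of *Analysis of secondary endpoints* correlates changes in fitness with changes in integrity, which treats both as continuous. Two paragraphs later, integrity and the fitness measures are dependent variables in logistic models. In the same section, logistic regression for transfer is correctly matched to a binary outcome.

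**Step 3: can the model be run as stated?** A standard binary logit was tried on a simulated continuous outcome with a mean of about 25. The software refused it because the response must lie in the unit interval.

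**Step 4: what a forced cut would cost.** The article gives no power figure for these models, so there is none to reproduce. For normal data and small effects, the asymptotic efficiency of a median split relative to the comparison of means is 2/π = 0.637, about 0.64.

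A finite-sample illustration uses these inputs:
- ACT group: 72 planned (*Sample size*); less 15% dropout, 72 × 0.85 = 61.2, taken as 61.
- Cologne participants who have cognitive training without ACT: 15 planned; with the same dropout (assumed here), 15 × 0.85 = 12.75, taken as 13.
- Effect: 0.5 SD, an assumption. Two-sided level 0.05, no covariates.

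*Continuous outcome.* Effect divided by its standard error: 0.5 / √(1/61 + 1/13) = 0.5 / 0.3055 = 1.637. Power ≈ Φ(1.637 − 1.960) = Φ(−0.323) = 0.37.

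*Median split.* The pooled median lies 0.414 SD above the control mean. The proportion above it is 0.339 in controls and 0.534 with ACT, a log odds ratio of 0.803. Its standard error is √[1/(13 × 0.339 × 0.661) + 1/(61 × 0.534 × 0.466)] = √(0.343 + 0.066) = 0.640. Power ≈ Φ(0.803/0.640 − 1.960) = Φ(−0.705) = 0.24. Simulation of the Wald test gives about 0.28; the gap arises because the formula is approximate with only 13 controls.

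At an assumed 0.8 SD and the same group sizes, simulated power is about 0.73 on the continuous scale and 0.56 after the split.

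**The case against.** **Integrity does have a high/low form.** *Primary objective* labels it so, the Fig. 2 legend sketches a threshold between stable transfer and non-transfer, and *Sample size* under Statistics speaks of equally sized integrity groups, which suggests a median split. This stands to a degree: a logistic model for high versus low integrity is imaginable. But the label is used for integrity as a predictor or subgroup of transfer, no cut-off value is given, and it covers one outcome of five.

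**A logit is not always impossible.** Fractional anisotropy lies between 0 and 1, so a fractional logit could run on it, and an ordinal logit could run on categorized outcomes. Neither is stated, and neither suits BDNF, oxygen uptake or test scores without rescaling or cutting.

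**It may be a slip for *linear*, or be corrected in an analysis plan that is not shown.** Both are possible, and for that reason it cannot be said that a post-hoc cut will happen. The article nevertheless names a specific model that does not match its outcomes. That is an incorrect statement, not an omitted detail.

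**A reader might infer that the secondary endpoints have no valid analysis at all.** The article does not support that. The correlation of fitness changes with integrity changes is a sound continuous analysis, and the models for transfer have a binary outcome. The secondary objectives in Table 1 all concern prediction of transfer.

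**The power figures are illustrative.** The effect sizes are assumed, the test is unadjusted, and the article specifies no median split. A larger comparison against all participants without ACT would be doubtful for the fitness measures, because *Study design* describes the fitness evaluation as a Cologne addition. The figures above therefore use Cologne participants only.

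**Conclusion.** The stated model type does not match the dependent variables in the ACT-effect models, nor in the baseline-activity models for integrity, Default Mode Network activity and BDNF. As written, these models do not fit their outcomes or require a dichotomy that the article does not specify. This conclusion rests on the text alone and needs no assumption about effect size.

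The cost of cutting is a matter of illustration: about 0.64 asymptotic efficiency for a median split, and roughly 0.37 against 0.28 power in the Cologne comparison at an assumed 0.5 SD. Power in that comparison is low either way, so correcting the model avoids a further loss but does not make the comparison well powered.

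The defect is confined to these models. The primary logistic regression, the logistic models for transfer and the correlation analysis are unaffected.

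**What to change.** In *Analysis of secondary endpoints*:

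1. For the ACT models, replace logistic regression with linear regression on the continuous outcome.
2. State the same for the baseline-physical-activity models, instead of leaving it to the reference to similar models.
3. Adjust for the pre-ACT value only where it is measured in both groups being compared. The pre-ACT phase is described only for the extended Cologne protocol, so participants without ACT may have no such value, and a general instruction to use baseline-adjusted models might not be workable.
4. Report mean differences for ACT, and regression slopes where baseline activity is analysed as a continuous measure, with 95% confidence intervals in natural or SD units.
5. Keep logistic regression for the binary transfer outcome.

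If a binary version of any outcome is really intended, its cut-off should be stated and justified before the data are analysed.

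The cost is a short change of text, with no additional data or participants. It does not settle the choice of covariates: each outcome is still adjusted for the others, which may themselves respond to ACT if measured after it, so the authors should check that set when they revise the paragraph.

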#### Secondary objectives

There is evidence that physical activity and cardiorespiratory fitness are associated with reduced brain tissue loss and reduced risk for cognitive impairment in aging humans [18, 19]. Moreover, aerobic exercise training increased gray and white matter volume in the prefrontal cortex [20] of older adults and led to significant improvements of executive function [21, 22]. Further, hippocampal and medial temporal lobe volumes were larger in older adults with greater cardiorespiratory fitness [19, 23], and larger hippocampal volumes mediated improvements in spatial memory [19]. Aerobic exercise training increases cerebral blood volume [24], perfusion [25] and the adult hippocampal volume. It has been suggested that the aforementioned structural changes are mediated by neurotrophins, in particular the brain derived neurotrophic factor (BDNF) [26]. We [27–30] and others [31, 32] demonstrated that exercise induces significant increases in levels of BDNF and other growth factors, and higher serum BDNF after aerobic training was associated with larger anterior hippocampal volume [33]. Using DTI, more recent studies measured brain structural integrity as a function of cardiorespiratory fitness and aerobic exercise training in HOA. Fractional anisotropy of the corpus callosum was reported to be positively correlated to cardiorespiratory fitness in HOA [34]. Thus, cardiorespiratory fitness might modulate age-related alterations of corpus callosum integrity. In addition, greater aerobic fitness derived from a walking program was associated with increases in white matter integrity of the frontal and temporal lobes, and improvement of memory performance [14]. Consistently, using resting state fMRI analyses, it has been shown that cardiorespiratory fitness is positively associated with functional connectivity in the Default Mode Network, and that this in part mediates improved performance on tasks requiring set-shifting, task switching, and spatial working memory [35]. Furthermore, 1 year of regular walking increased functional connectivity between parts of the frontal, posterior, and temporal cortices within the Default Mode Network and the Frontal Executive Network [35]. Of note, there is evidence that the beneficial effects of physical activity on cognitive performance is not limited to cardiorespiratory fitness but is also present after resistance [36–38] and coordination exercise training [39, 40]. Moreover, different types of physical training have been shown to affect different neurocognitive networks [40, 41]. We hypothesize that coordination exercise training positively modulates cognitive transfer abilities in HOA based on the following rationale: coordination training aims at improving the efficiency of complex body movements including eye-hand coordination, bimanual coordination, leg-arm coordination, and reactions to moving objects [40]. Such complex movements require bihemispheric interactions via the corpus callosum [42], and both, size and structural integrity of the corpus callosum typically change after sensorimotor skill acquisition [43]. These interactions are probably not limited to pure motor processes but rather include selective aspects of cognition necessary for adaptive motor behavior such as attention, inhibitory and facilitatory processes, working memory, and error-related processing. In line with this, it has been demonstrated that rather anterior corpus callosum projections to the prefrontal cortex than middle corpus callosum projections to the primary motor cortex predict bimanual motor learning [44].

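### The ACT-impact models adjust each outcome for the other ACT outcomes, so the ACT coefficient is at best a direct effect and not the impact of ACT

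*Protocol article*

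**What the plan says.** Under Analysis of secondary endpoints, the Protocol article gives the purpose of one family of models: "To determine the impact of ACT on the structural integrity of the corpus callosum, Default Mode Network activity, BDNF, motor fitness, and VO_2_peak/VO_2_max". ACT enters each model as an independent variable. The adjustment rule follows: "Additionally, the model will be adjusted for all other variables and the interactions with ACT". A worked example removes doubt about what the other variables are: "the model for structural integrity of the corpus callosum will include ACT, Default Mode Network activity, BDNF, motor fitness, VO_2_peak/VO_2_max and all interactions". No model with ACT but without the other four outcomes is described for any of the five. The correlation between fitness change and integrity change, in the same section, does not compare ACT with no ACT.

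The rationale is under Secondary objectives. On fitness: "cardiorespiratory fitness might modulate age-related alterations of corpus callosum integrity". On motor learning: "size and structural integrity of the corpus callosum typically change after sensorimotor skill acquisition". On exercise-induced structural change in general, it reports the suggestion that such "structural changes are mediated by neurotrophins, in particular the brain derived neurotrophic factor (BDNF").

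ACT is given only in Cologne, to 72 recruited subjects. Another 15 Cologne subjects follow the standard protocol without it (Population, Sample size).

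**The concern.** The impact of an intervention on an outcome is its total effect, whatever the route. Once variables that the intervention may itself change are held fixed, the coefficient covers only what does not pass through them. Here the covariates for each outcome are the remaining targets of the same intervention, and the protocol gives biological reasons why several of them could carry the effect on the callosum. Including every ACT interaction adds a second difficulty: the ACT coefficient then refers to one set of covariate values and is no longer an overall effect.

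At stake is the reading of variables that the Abstract names as secondary endpoints. If ACT improves callosal integrity partly by improving fitness, the planned coefficient will understate that improvement, and a non-significant result could be taken as evidence that ACT does nothing. Allocation within each site is described as random, so the comparison within Cologne could support a causal statement. Conditioning on variables measured after allocation gives that up.

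**Working it through.** The plan gives no effect size, power or sample size for these models, so there is no figure to reproduce. The size of the problem can only be shown under assumptions.

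**Inputs from the Protocol article**
- ACT subjects evaluable: 60 (Statistics, Sample size).
- Non-ACT subjects if all sites are used: 160 − 60 = 100.
- Non-ACT subjects within Cologne: 15 recruited; 15 × 0.85 = 12.75, about 13 after 15% dropout.
- Significance level 0.05. Sidedness is not stated; two-sided is used here.

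**Assumptions, not in the documents**
- Total ACT effect on the outcome: 0.5 within-group SD.
- Each of the four covariates is shifted 0.8 SD by ACT.
- A share m of the total effect runs through the covariates, split equally, with m from 0 to 1.
- Linear models, although the plan says logistic, because the article does not say how these variables would be dichotomised. Covariates are centred at the sample mean.

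**Model.** With A for ACT, each covariate is M = 0.8·A + noise, and the outcome is Y = (1 − m)·0.5·A + b·ΣM + residual, where b = m·0.5/(4 × 0.8). The indirect part is 4 × b × 0.8 = 0.5m and the direct part is 0.5(1 − m), so the total is always 0.5. For m = 0.5, b = 0.25/3.2 = 0.078, and direct and indirect parts are 0.25 each. A model that conditions on the four covariates targets 0.5(1 − m).

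**Unadjusted power by hand.** For 60 versus 100, SE = √(1/60 + 1/100) = 0.163; 0.5/0.163 = 3.06; power = Φ(3.06 − 1.96) = Φ(1.10) = 0.86. For 60 versus 13, SE = √(1/60 + 1/13) = 0.306; 0.5/0.306 = 1.63; power = Φ(−0.33) = 0.37. The simulation gave 0.36.

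**Simulation, 3000 replicates.** The adjusted model has all four covariates and their ACT interactions.

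| Mediated share | Coefficient, unadjusted | Coefficient, adjusted (60 vs 100) | Power, unadjusted / adjusted (60 vs 100) | Power, unadjusted / adjusted (60 vs 13) |
|---|---|---|---|---|
| 0% | 0.50 | 0.50 | 0.86 / 0.61 | 0.36 / 0.16 |
| 25% | 0.50 | 0.37 | 0.86 / 0.38 | 0.36 / 0.11 |
| 50% | 0.50 | 0.25 | 0.86 / 0.21 | 0.36 / 0.08 |
| 75% | 0.50 | 0.12 | 0.86 / 0.09 | 0.36 / 0.07 |
| 100% | 0.50 | 0.00 | 0.86 / 0.05 | 0.36 / 0.06 |

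Even with no mediation, adjustment costs power, because covariates that ACT shifts are correlated with ACT and inflate its standard error.

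**The reverse direction.** With VO2 as the outcome, some covariates lie downstream of it. Suppose ACT raises VO2 by 0.5 SD and each of four downstream variables correlates c with VO2 within group. Without interactions, the adjusted ACT coefficient is 0.5/(1 + 4c²/(1 − c²)). For c = 0.2 this is 0.5/1.167 = 0.43; for c = 0.6 it is 0.5/3.25 = 0.15. The simulation agrees. These covariates are not routes to VO2, yet adjusting for them still distorts the ACT effect.

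**The case against.** The best defence is that the covariates could be pre-ACT values, which would remove the problem. The section does not say when they are measured. However, they are the same variables on which an ACT impact is sought, and the following paragraph says baseline where baseline is meant. If pre-ACT values were intended, the wording still needs to say so.

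Second, the rationale is hedged. Fitness only might modulate callosal integrity. The BDNF sentence refers to structural changes listed before the callosum is discussed. Network activity is a route to cognition and not to the callosum: "cardiorespiratory fitness is positively associated with functional connectivity in the Default Mode Network, and that this in part mediates improved performance". All this stands, and it limits how firmly any one covariate can be called a mediator. It does not turn an estimate conditional on other ACT outcomes into a total effect.

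Four stronger readings are tempting, and the documents do not support them:
- A reader might infer that a real ACT effect must be adjusted to zero. That needs full mediation, and no mediated share is given.
- A reader might size the loss with the correlation of 0.43 from the Sample size paragraph. It is unclear whether that figure links fitness change to integrity change or to degree of transfer, so it is not used here as a fitness-to-callosum path.
- A reader might say that the interactions place the ACT coefficient at VO2 = 0 and BDNF = 0. That assumes uncentred covariates, and an article commonly leaves coding to the analysis plan.
- A reader might extend the point to the baseline-physical-activity models. Those are described as examining an association, for which a conditional estimate is a legitimate target.

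Finally, the primary analysis is unaffected, as are the two ACT analyses that have a sample-size rationale: the correlation of fitness change with integrity change, and the interaction on transfer. The impact of ACT on these five variables is also not listed among the objectives in Table 1. This bears on severity, not on correctness.

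**Conclusion.** The point holds for the ACT-impact models. As written, they do not estimate the quantity they are introduced to estimate. The loss is partial or total according to the mediated share: in the illustration, from none to all of an assumed 0.5 SD effect, with adjusted power between 0.61 and 0.05 against 0.86 for 60 versus 100, and between 0.16 and 0.06 against 0.36 for 60 versus 13. The Study design section places the fitness evaluation in the extended Cologne protocol, so the smaller comparison may be the relevant one for any model containing VO2 or motor fitness. The figures rest on the assumed effect, the assumed 0.8 SD shifts and linear models; the direction of the argument does not rest on those values. The point should be fixed, but it is not critical, because it concerns secondary endpoints.

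**What to change.** In the ACT-impact models, remove the other post-ACT outcomes and their ACT interactions. Estimate each ACT effect with pre-intervention covariates only: age, sex, and the pre-ACT value of the outcome where it was measured. The last is usable in a group comparison only if the non-ACT subjects have a corresponding measurement. Mainz and Rostock have no pre-ACT phase, and the article text does not settle the matter for the 15 Cologne controls.

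State the comparison. Either use ACT versus no ACT within Cologne and accept its low power, or include the other sites and say plainly that ACT is then confounded with centre. If pathways are of interest, report mutually adjusted models as a separately labelled exploratory mediation analysis.

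The cost is a change of analysis wording and a decision on the comparison group. No new data are needed, and the models become smaller. The choice of comparison does limit what can be claimed, since rewording cannot enlarge the Cologne control group.
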